As, to the best of our knowledge, this is the first study using a sequential design with two intensive meditation modalities, it is difficult to formulate specific hypotheses regarding the separate and combined effects of the MBSR and CCT programs on the selected outcomes. Thus, considering the two MBIs jointly, we expect that both programs will significantly: a) modify the DNA methylation and expression levels of specific genes and a reduction of the DNA methylation-based biological clock; b) reduce participants’ levels of psychological distress while increasing their levels of psychological functioning (i.e., mindfulness, compassion, emotion regulation, and well-being); c) change the EEG spectral profile of the resting state brain activity (i.e., changes in the balance between Alpha (8–14 Hz) and Theta (4–8 Hz) frequency bands and, regarding the organization of the brain functional networks, a modulation of the difference between the activation of the default mode network and the one corresponding to the salience network); d) alter awakening and bedtime cortisol levels leading to a steeper Diurnal Cortisol Slope (DCS); e) improve the efficacy of mood regulation following a negative mood induction (using an autobiographical memory task); f) reduce participants’ reactivity in an objective experimental stress test (i.e., Arithmetic Stress Test). In addition, given the multidisciplinary nature of the present project, we intend to provide a comprehensive view of potential changes in various areas of biological and psychological functioning and their interrelationships.

In general, we expect an overall pattern of results in which changes will be significantly higher for the combined effects of both MBIs than for each program separately. Moreover, based on previous literature comparing standard MBSR and CCT programs [24], we expect no major differences in primary outcomes between both programs, although the mechanisms of change may be different; in general, changes in MBSR will be mediated by cognitive variables (e.g., mindfulness) whereas changes in CCT will be mediated by socio-emotional variables (e.g., compassion). We also expect that the self-reported psychological changes associated with the MBIs will remain 3 months after the programs.

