** *Epigenetic measures* **					
• DNA methylation levels		x	x	x	
• Proportion of main blood cell types		x	x	x	
• Epigenetic clocks		x	x	x	

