### 2.7 Statistical analysis plan

Independent t-tests for continuous data and chi-square test (χ2) for categorical data will be conducted to confirm that there were no demographic or clinical differences between groups at baseline. Repeated-measures ANOVAs will be conducted to analyse changes associated with the programs. For the autobiographical memory task and all the biological measures (i.e., genetic measures, EEG, EKG, respiratory rate, and cortisol in saliva), a 2 (Order of program) x 3 (Time) repeated measures ANOVA will be conducted. For the self-report psychological measures, a 2 (Order of program) x 4 (Time) ANOVA will be conducted. We will use age, sex, and previous meditation experience as covariates in the main analyses. Assumptions of normality, homogeneity of variances, sphericity, and homogeneity of covariances will be checked. Further analyses will include post-hoc, p-corrected comparisons (e.g., Bonferroni). All analyses will be performed with SPSS 28.0 (IBM Corp., 2021) or R Studio statistical software (R Core Team, 2021). Two-tailed tests will be used to determine significance at the 5% level.

The EPIC methylation arrays´ raw data will be normalised and filtered by a robust bioinformatics pipeline procedure [69]. We will then perform an unsupervised analysis of the data via hierarchical clustering, i.e., PCA and t-SNE (by R Studio). In parallel, taking advantage of the known DNA methylation signatures related to distinct cell types or molecular processes, we will: 1) characterize the proportion of different immune cells, and 2) determine the epigenetic age with Horvath’s model or other epigenetic clocks to capture the influence of lifestyle on the DNA methylome [70, 71]. This may reveal a link between the MBI programs and the immune response, inflammation, and cells’ physiological condition. Finally, we will focus on supervised analyses to identify differential DNA methylation biomarkers in the two groups (MBRS first *vs* CCT first) and time points: day 1(baseline), day 4 (program switch), and day 7 (post retreat).

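### Section 2.7 states no adjustment of the methylation and clock analyses for the immune-cell proportions it estimates, so a change over time could reflect a shift in cell mix

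*Protocol article*

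**What the plan says.** Under Epigenetic changes (2.5.1), mononuclear cells are isolated from peripheral blood by gradient centrifugation. This is a mixed fraction, not one sorted cell type. Table 2 lists "Proportion of main blood cell types" among the epigenetic measures, on days 1, 4 and 7.

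The first paragraph of section 2.7 assigns the biological measures, with genetic measures named among them, to one model: "a 2 (Order of program) x 3 (Time) repeated measures ANOVA will be conducted". It then states: "We will use age, sex, and previous meditation experience as covariates in the main analyses".

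The array paragraph of section 2.7 runs in sequence: normalising and filtering by a cited pipeline, then unsupervised analysis. In parallel, the team will "characterize the proportion of different immune cells" and "determine the epigenetic age with Horvath’s model or other epigenetic clocks". Last, "we will focus on supervised analyses to identify differential DNA methylation biomarkers in the two groups" and across the three days. The only purpose given for the cell proportions is descriptive, as a possible sign of an immune response.

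Hypothesis (a) in the Introduction expects changed methylation and expression of particular genes, and "a reduction of the DNA methylation-based biological clock".

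**The concern.** In a mixed sample, the methylation measured at a site is an average over cell types, weighted by their proportions. If the proportions move between days, the measured value moves at every site where the cell types differ, even when no cell changes its methylation. A time effect then has two explanations: change inside cells, which is what hypothesis (a) claims, and redistribution of cells.

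Randomisation does not separate them for the time effect, because everyone attends the same retreat. The Discussion concedes that silence and rest may contribute to whatever changes are found. It also reads earlier reports of immune-related methylation change as evidence that meditation had an effect. A change in immune-cell mix could produce an immune-related pattern too. The ambiguity would carry into the planned mediation question and into the correlations of epigenetic change with EEG and psychological change.

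**Working it through.** The protocol gives no figure on this point, so there is nothing to reproduce. The check has a textual part and an illustrative part.

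**Text.** Three statements of the article, set side by side:

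1. The cell proportions are available on all three sampling days (Table 2).
2. Their stated use is as an output alongside the clocks (2.7, array paragraph).
3. The covariates for the main analyses are age, sex and previous meditation experience (2.7, first paragraph). For a given person these are constant over the 7 days, so they cannot account for a within-person change in cell mix.

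No section uses the proportions as a covariate, residualises methylation or clock values on them, or plans a sensitivity analysis with them.

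**Illustration at one site.** From the protocol: n = 52 and two-sided 5% tests. Assumed, because the documents give no values: the mean shift s in one cell type, the difference D in methylation between that cell type and the rest, and the within-person SD of change.

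Spurious mean change = s × D. Test statistic t = (s × D) / (SD / √52), with √52 = 7.21.

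| s | D | s × D | t at SD 0.02 | t at SD 0.03 |
|---|---|---|---|---|
| 0.03 | 0.6 | 0.018 | 6.5 | 4.3 |
| 0.01 | 0.6 | 0.006 | 2.2 | 1.4 |

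The 1-point row corresponds to p = 0.035 and p = 0.16 on 51 degrees of freedom.

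**Simulation.** 52 people and one site with no true change inside any cell type. Assumed: individual shifts with SD 0.04, residual SD 0.02, D from 0.3 to 0.8, and 1,500 runs per setting. The unadjusted analysis is a one-sample t-test of the change. The adjusted analysis tests the intercept of a regression on the change in cell proportion.

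| Mean shift | Unadjusted rejection | Adjusted rejection |
|---|---|---|
| 1 point | 14–32% | 4.5–5.1% |
| 2 points | 44–85% | 3.7–4.8% |
| 3 points | 78–99% | 4.3–5.9% |
| 5 points | over 99% | 4.9–5.9% |

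The simulation treats the proportions as known without error. Proportions estimated from the arrays would remove somewhat less of the bias.

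**Multiplicity.** Both illustrations use a single-site threshold. If 100,000 to 900,000 sites were Bonferroni-corrected (an assumed count), the two-sided threshold is 0.05/100,000 = 5.0 × 10⁻⁷ to 0.05/900,000 = 5.6 × 10⁻⁸, which on 51 degrees of freedom means |t| of about 5.8 to 6.4. Of the four values in the first table, only 6.5 passes.

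**Which contrasts are exposed.** A shift s common to both order groups adds s × D to the change over time in each group. It cancels in the difference between groups: s × D − s × D = 0. If the shifts are s₁ and s₂, the order-by-time contrast is biased by (s₁ − s₂) × D, which is zero unless they differ.

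**The case against.** The strongest objection is that the text is silent rather than wrong. The array paragraph gives no model for the supervised step. The covariate sentence stands in the preceding paragraph, directly after the ANOVAs, and may not have been meant as a closed list for site-level models. Array handling is delegated to a cited pipeline that cannot be inspected here, and a journal article may leave such detail to a fuller plan. Part of this stands. A reader might infer that the investigators have decided against adjustment. The documents do not support that: they state no adjustment, but they do not exclude one in the supervised step or in the pipeline. Yet the article does more than stay silent. It counts genetic measures among the ANOVA outcomes, names covariates, gives the cell proportions a different role, and credits the pipeline only with normalising and filtering.

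A second objection is that safeguards exist. Proportions are obtained on every sampling day, so a shift would be visible. Isolating mononuclear cells narrows the mix, and fixed morning appointments limit time-of-day variation. All true, but seeing a shift does not remove its contribution from the site-level results, several cell types remain, and a fixed hour does not prevent a shift caused by the retreat.

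Third, a change in cell mix may itself be an effect of the programs, and adjustment would hide it. This stands, and is why both models should be reported.

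Fourth, cell adjustment does not supply the missing non-retreat control. That is also correct: it separates change within cells from change in mix, not program from retreat.

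**Conclusion.** The point holds in a limited form. Followed as written, section 2.7 cannot tell whether a day 1, 4 and 7 time effect on methylation reflects change within cells or a change in cell mix, and hypothesis (a) needs that distinction. It should be settled before analysis, so that the choice between adjusted and unadjusted results is not made after seeing them.

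Three stronger readings are tempting and not supported:

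- **That all the epigenetic comparisons are biased.** A common shift affects mainly the time effect. Order and order-by-time contrasts are affected only if the shift differs between the order groups.
- **That the clock is equally exposed.** Its sensitivity to cell mix depends on the clock, which section 2.7 leaves open, and no calculation here covers it.
- **That the false-positive rates above predict this trial.** The documents give no cell shift, between-cell difference or SD. The figures show the mechanism at a single site, and the smaller shifts would not survive array-wide correction. Such correction controls chance findings; it would not remove a systematic bias large enough to pass.

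**What to change.** Add to section 2.7: the supervised methylation models and the clock models will be fitted with and without the cell proportions estimated at the same time point, entered as time-varying covariates, and both sets of results will be reported. Claims of gene-specific change will rest on the adjusted model. Effects seen only in the unadjusted model will be described as consistent with a change in cell mix, which may itself be a program effect. If the cited pipeline already adjusts for cell mix, a sentence saying so would answer the adjustment point; the unadjusted results are still worth showing beside it.

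The cost is a short addition to the text, one extra model run and a few degrees of freedom. No new sampling is needed, because Table 2 already plans the proportions on all three days.

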#### 2.5.3 Neurobiological laboratory measures

*a) Brain electrical activity*. Recording of EEG activity in resting state (alternating open and closed eyes, 6 min each condition) with four EE-225 64chEEG+24chBIP 16kHz devices with a laptop and eego EEG recording software. The sampling rate will be set at 1000 Hz and the reference is 7Z of the equidistant layout.

*b) Respiratory activity*. Respiration rate, which is related to attention training and psychological well-being [67], will be monitored by a respiration chest-band, during the EEG assessment session and will be registered using a piezoelectric sensor.

*c) Cardiac activity*. EKG activity will be monitored with dedicated electrodes during the EEG assessment session. Based on these recordings, we will analyze changes in EKG, heart rate, and heart rate variability (HRV) patterns

These recordings will be completed by everyone in laboratory spaces dedicated to the EEG assessments.

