The EEG signals will be assessed both at the sensor level and the source’s space. Source space reconstruction would be performed using the eLoretta procedure over the MNI template. The analysis will be conducted two-fold: 1) the power spectral profiles of each condition (eyes closed and eyes open) will be computed using the fast Fourier transform algorithm; 2) the functional networks will be calculated using a phase synchronization algorithm (i.e., phase locking value). The functional networks will be created using standard regions of interest defined over the AAL atlas.

Diurnal Cortisol Slope (DCS) will be calculated individually for each participant as a function of their respective bedtime and awakening times. DCS will be calculated as awakening cortisol subtracted from bedtime cortisol, divided by each subject’s total waking hours.

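### EEG networks are computed with the phase locking value on regions reconstructed from 64 channels, a measure that a change in alpha power can shift with no change in coupling

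*Protocol article*

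**What the plan says.** Hypothesis c in section 1 has two EEG parts. One is spectral: "changes in the balance between Alpha (8–14 Hz) and Theta (4–8 Hz) frequency bands". The other concerns functional networks: "a modulation of the difference between the activation of the default mode network and the one corresponding to the salience network". No direction or size is given for the spectral change, and no frequency band for the network change.

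Section 2.5.3 describes the recording: "four EE-225 64chEEG+24chBIP 16kHz devices with a laptop and eego EEG recording software", at rest, "alternating open and closed eyes, 6 min each condition".

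Section 2.7 describes the analysis. "Source space reconstruction would be performed using the eLoretta procedure over the MNI template". Power spectra come from a Fourier transform, and "the functional networks will be calculated using a phase synchronization algorithm (i.e., phase locking value"). The nodes of these networks are taken from a standard atlas: "The functional networks will be created using standard regions of interest defined over the AAL atlas"; the number of regions is not given. EEG outcomes go into a 2 (order) x 3 (time) repeated-measures ANOVA. The covariates for the main analyses are age, sex and previous meditation experience; band power is not among them.

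**The concern.** PLV is the length of the average phase difference between two signals. It does not distinguish two regions that are coupled from two regions that both contain a share of the same source. After reconstruction from scalp EEG the second situation is always present to some degree, and it shows up at zero lag.

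A fixed head model keeps the mixing weights constant over days 1, 4 and 7. That protects the comparison over time only if the relative power of the sources also stays constant, and hypothesis c expects a change in relative band power. A network change over Time, or between orders, might then be partly the spectral change seen through a second measure. The two parts of hypothesis c would be weaker as separate evidence than they appear. The planned correlation of epigenetic change with change in brain activity (section 3) would inherit the same ambiguity wherever PLV is used.

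**Working it through.** The plan states no figure to reproduce, so the check is of the mechanism and its possible size.

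**Inputs from the article:** 64 channels and 6 min per eye condition (2.5.3); alpha 8–14 Hz, a 6 Hz band (1); eLORETA, AAL regions and PLV (2.7).
**Assumed:** 90 regions (90–116 considered), head model, strength and location of alpha, noise level.

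**1. Rank.** Average referencing leaves 64 − 1 = 63 independent channels. With 90 regions, at least 90 − 63 = 27 region signals are linear combinations of the others. Leakage does not depend on this count, but the count shows that some mixing is unavoidable.

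**2. Mechanism by hand.** Take two regions, each with its own independent source of power 1, both receiving one strong source of power P at relative weight w. True coupling between the two local sources is zero.
- Coherence = w²P / (1 + w²P).
- With w = 0.24 (median relative leakage among the five nearest regions in simulation B below) and P = 16 (4x amplitude): 0.922/1.922 = 0.48.
- With power up 50%, P = 24: 1.382/2.382 = 0.58.

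For Gaussian signals PLV rises with coherence. If all sources scaled together, the ratio would not change: alpha must rise relative to background. A two-region simulation with leakage 0.4 agrees. Without noise PLV stays at 0.598 at every power level; with local noise it goes 0.507, 0.534, 0.548 at power x1, x1.5, x2.

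**3. Whole-network simulations, all sources independent.** The chance floor is √(π/(4T)) with T = 360 s x 6 Hz = 2,160, giving 0.019. Change in mean PLV over all region pairs:

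| Simulation | Alpha power | Mean PLV | Change |
|---|---|---|---|
| A: three-shell head, 12 posterior sources, 4x amplitude | +50% | baseline 0.07–0.09 | +18% to +19% |
| A, same | −30% | | −9% to −10% |
| B: homogeneous sphere, 31 posterior sources | +20% | 0.0629 → 0.0665 | +6% |
| B | +50% | 0.0629 → 0.0713 | +13% |
| B | +100% | 0.0629 → 0.0784 | +25% |
| C: 4x amplitude | +50% | 0.0516 → 0.0634 | +23% |
| C: 2x amplitude | +50% | 0.0379 → 0.0393 | +4% |

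In B, PLV between the true sources stayed at 0.0196–0.0197 throughout, and replicate SD for the reconstructed mean was about 0.001. Which pairs move depends on the set-up. In B at doubled power, pairs of regions without an alpha source rose from 0.0697 to 0.0967 (+39%), and pairs within the posterior set hardly moved (0.0799 to 0.0805). In A at 2x amplitude, only pairs touching posterior regions rose (+0.010 to +0.012).

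**4. A zero-lag-insensitive companion on the same data.** With z the mean phase-difference vector, PLV = |z| and corrected imaginary PLV = |Im z| / √(1 − (Re z)²). In B it went from 0.0137 to 0.0140 at +50% power; in A it moved by less than 0.001; in C it stayed at 0.012.

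**5. What the companion does not remove.** With fixed lagged coupling (0.5, lag π/4), local noise equal to signal and power raised 50%, PLV went from 0.199 to 0.240 (+21%) and corrected imaginary PLV from 0.143 to 0.170 (+19%). A repeat gave 0.142 to 0.171 (+20%). Higher power improves signal-to-noise ratio, and both measures respond to that.

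**The case against.** The strongest reply is that a journal article gives EEG only a few sentences and a fuller plan may contain leakage control. That stands for what is merely unsaid. The article does not state that PLV is the only measure, and it uses the abbreviation before it loosely elsewhere. It also stands for recording quality: a reader might infer that unequal amounts of clean data between days would bias PLV, but the article sets the same recording length for every session, and epoch selection is detail it may leave out. It does not answer the point about the estimator, which the article names.

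Second, hypothesis c gives no direction for the spectral change, and a change in theta alone could satisfy it. This stands. A reader might infer that any network finding will simply be the alpha result reported again; the documents support only that this could happen.

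Third, the simulated quantity is mean PLV over region pairs, and the hypothesis concerns the difference between two networks. Leakage that raises both may partly cancel; a rough check with an approximate head model was mixed, cancelling on average with strong alpha but not with weak alpha, and varying with node choice. The percentages above therefore must not be read as the bias in that contrast. Nor is a false-positive rate shown, since between-participant variance and the ANOVA were not modelled. For an Order x Time effect, alpha would also have to change differently by order.

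Fourth, power spectra from the same recordings will be reported, so a reader can see whether power moved. That helps, but does not show how much of a PLV change power explains.

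**Conclusion.** The point holds as a weakness in the stated network measure. PLV on eLORETA-reconstructed atlas regions from 64 channels can shift with alpha power at zero true coupling. The range of about +4% to +23% in mean PLV for +50% posterior alpha power rests on assumed alpha strength, head model, noise and 90 regions. The direction of the mechanism does not rest on those choices, provided alpha changes relative to background and leakage is left uncorrected.

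The documents do not support saying that the network result will be an artefact, that the default-mode versus salience contrast is biased by any given amount, or that agreement with a zero-lag-corrected measure would prove a change in coupling. Such agreement removes the leakage route and leaves the signal-to-noise route open. The consequence is limited to interpretation of the network part of hypothesis c and of analyses built on it.

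**What to change.** In section 2.7:
- Keep PLV as the network measure.
- Add a zero-lag-insensitive companion, such as corrected imaginary PLV or the weighted phase lag index, on the same reconstructed signals, labelled a sensitivity analysis.
- Repeat the network Time and Order x Time contrasts with adjustment for the change in band power.
- State in advance that a network change seen only in PLV, or one that disappears after power adjustment, will be described as possibly power-driven.

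The cost is analysis code and a few lines of text; no new data or participants are needed. The companion misses true zero-lag coupling, is noisier and remains sensitive to signal-to-noise ratio, so it supports PLV and should not alone decide whether a network change is claimed. Band power is measured after the programs begin and may itself respond to them, so the adjusted contrast is an aid to interpretation and not a replacement for the main one.

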### 2.3 Sample size

According to G*Power software, we need 21 participants per group to obtain a power of .95 to detect a mean effect size of .37 (based on well-being outcomes in mindfulness retreats, [11]), using order of intervention as a between-subject factor (MBSR first vs CCT first) and time as a within-subjects factor (5 times of assessment), with an alpha of .05, a power 95%, and a 2-tailed test. In anticipation that there may be last-minute dropouts in pre-registrants or incomplete data in the sample collection or the analysis of the planned psychological or biological data, we have increased the sample by an additional 20% to 26 participants for each condition (52 in total). This sample size further corresponds to the average size of standard meditation retreats [11, 41] and in studies of brain activity in meditators [29, 30].

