Intention-to-treat (ITT) analyses will be conducted with all participants, regardless of session or outcome measure completion. The pattern and percentage of missing data will be explored before analysing the data. It should be noted that the chances of missing data will be minimized because the questionnaire administration format via Qualtrics does not allow progress to be made until all items in each questionnaire are completed. Binary logistic regression will be used to evaluate the assumption that data is Missing at Random (MAR). ITT mixed models (restricted maximum likelihood (REML) estimation) will be used to account for missing data MAR. If missing were not random (MNAR), we would conduct Multiple Imputation and Pattern Mixture Models incorporating the predictor responsible for the missingness into the model. In any case, sensitivity analysis will be performed, comparing the main outcomes between completers and imputed values. To safeguard the confidentiality of participants’ data, all samples will be anonymized with alpha-numeric codes. These codes will not carry any personal information. Personal data linked to the alpha-numeric code will not be included in any files used for data analyses and will remain separate from the main database. Data displayed in public repositories (e.g., GitHub or datadryad.org), linked to the resulting publications, will always be anonymized. Data supporting each published study will be included within the article and/or supporting materials. To improve blinding integrity [72], personnel who will analyse the data collected from the study are not aware of the treatment applied to any given group. The authors will be fully responsible for handling and analyzing data independently from any sponsor. All the questionnaires included in the protocol as well as a copy of the informed consent, are available at https://osf.io/gczas/?view_only=7864451a24cf4a82824f6f298b1bbf0f.

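### The MNAR analysis is run only if a logistic regression points to MNAR, but that regression cannot tell MAR from MNAR

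*Protocol article*

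**What the plan says.** Section 2.7 (Statistical analysis plan) of the protocol article sets out a sequence for missing data.

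1. The analysis set is everyone randomised: "Intention-to-treat (ITT) analyses will be conducted with all participants, regardless of session or outcome measure completion".
2. The pattern and percentage of missing data are explored first. Then the mechanism is assessed: "Binary logistic regression will be used to evaluate the assumption that data is Missing at Random (MAR").
3. For MAR data, "ITT mixed models (restricted maximum likelihood (REML) estimation) will be used to account for missing data MAR".
4. If missingness is found not to be random (the article's label is MNAR), "we would conduct Multiple Imputation and Pattern Mixture Models incorporating the predictor responsible for the missingness into the model".
5. Whatever the outcome of these steps, "sensitivity analysis will be performed, comparing the main outcomes between completers and imputed values".

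Section 2.1 and Table 2 add that the 3- and 12-month follow-up uses self-report questionnaires only, and section 2.1 that these are completed online. Section 1 predicts that self-reported changes will persist at 3 months. It states no such prediction for 12 months.

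**The concern.** Step 2 asks the regression a question it cannot answer, and step 4 depends on the answer. A logistic model for missingness can only use variables that were recorded. Whether missingness also depends on the values that were not recorded, which is what separates MNAR from MAR, leaves no trace that such a model can identify.

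The wording of step 4 adds to the difficulty. A predictor that can be found and entered in a model is an observed one, and missingness explained by it is MAR given that predictor. The plan nevertheless places it under the MNAR heading.

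The follow-up self-reports are the outcomes at stake. On days 1, 4 and 7 participants are resident at the retreat. At 3 and 12 months they are at home answering online, and the decision to reply may depend on how they feel. The forced-completion setting in the questionnaire software prevents skipped items but not failure to reply at all. Both orders receive both programs and there is no untreated arm, so persistence is judged as change within persons. Bias from outcome-related non-response then has no control arm against which it could cancel.

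**Working it through.** The article states no figure on this point, so there is none to reproduce. The check has three parts.

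**1. Logic of the rule.** Let R be the missingness indicator, X the observed data and Y the unobserved outcome.

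- MCAR: P(R | X, Y) = P(R).
- MAR: P(R | X, Y) = P(R | X).
- MNAR: P(R | X, Y) still depends on Y once X is given.

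Logistic regression estimates P(R | X). If X predicts R, that is evidence against MCAR and is compatible with both MAR and MNAR. If X does not predict R, that is compatible with MCAR and also with MNAR. Neither result bears on MAR against MNAR.

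**2. Simulation.** The inputs from the article are 52 participants, 26 per order (section 2.3), and a 5% significance level (section 2.7). The other inputs are assumptions:

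- about 20% missing;
- baseline-outcome correlation 0.5;
- missingness log-odds slope of 1 per SD;
- true mean 0.

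Missingness was regressed on baseline and order, with a 2-df likelihood-ratio test. The mean was then estimated under MAR by regression imputation on baseline. There were 2,000 runs at n = 52 and 500 runs at n = 500.

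| True mechanism | Test significant, n = 52 | Test significant, n = 500 | Bias of MAR estimate (SD) |
|---|---|---|---|
| MCAR | 6.6% | 4.8% | 0.00 |
| MAR (depends on baseline) | 66% | 100% | 0.00 |
| MNAR (depends on outcome) | 20% | 96% | about -0.14 |
| MNAR (depends on the part of the outcome unrelated to baseline) | 6.6% | 6.4% | about -0.15 |

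The biases are nearly the same at both sample sizes. Their sign follows from the simulated direction, in which higher values were more often missing. Three things follow.

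- The test is significant most often under MAR, where the MAR estimate is already unbiased.
- In the last row it behaves as it does under MCAR, and a larger sample does not help.
- The MAR estimate already uses the observed baseline value, so putting an observed predictor in the model leaves the MNAR bias in place.

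**3. Illustrative size at follow-up.** Bias in the mean = proportion missing x departure of non-responders from their MAR prediction. Both inputs are assumptions: 20% missing, and non-responders 0.25 to 0.75 SD worse.

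- 0.20 x 0.25 = 0.05 SD
- 0.20 x 0.50 = 0.10 SD
- 0.20 x 0.75 = 0.15 SD

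The bias is proportional to non-response. At half that rate (10%) the range is 0.025 to 0.075 SD.

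**The unconditional sensitivity analysis.** Comparing complete cases with imputed data contrasts two treatments of the missing values. As stated, neither side assumes a departure from MAR. Agreement between them would not be evidence against MNAR.

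**The case against.** The strongest reply is that the plan does name an MNAR-capable method. A reader might infer that MNAR is answered with a MAR method alone, or that MNAR dropout is never examined. The text does not support that: the sentence that names multiple imputation also names pattern-mixture models, a standard approach to MNAR. What remains is that they are run only after a test that cannot identify MNAR, and that the description, an observed predictor added to the model, leaves open whether they would go beyond MAR.

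A second reply is that the article does not say how the pattern-mixture models are identified because an article condenses. That is fair. The identifying assumption may stand in a full protocol or analysis plan that is not shown, and its absence is not the criticism. The criticism is of the decision rule, which the article does state.

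Third, the article says only that the regression evaluates MAR. It nowhere says that a non-significant result proves MAR, or that every significant predictor will be labelled MNAR. Those are the natural readings of the sequence, not explicit commitments. But no other criterion for judging the data MNAR is given.

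Fourth, the reach is limited. The epigenetic, EEG, EKG, cortisol and stress-task outcomes are collected only during the retreat, so the argument about replying from home does not touch them. No sample size, power or alpha figure depends on this point. All of this stands.

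**Conclusion.** The point holds for the decision rule. A regression on observed variables is used to evaluate MAR, and the only analysis that could address MNAR depends on the result. That rests on the definitions and needs no numerical assumption. The simulation shows how the rule could behave at this trial's size, and its percentages depend on the assumed correlation, slope and missing rate.

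The 0.05 to 0.15 SD is an illustration, not a forecast. Two stronger readings should be avoided.

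- The 20% is not a follow-up non-response rate taken from the plan. Section 2.3 says "we have increased the sample by an additional 20% to 26 participants for each condition (52 in total"), and that allowance covers late dropouts among pre-registrants and incomplete collection or analysis of data.
- The bias should not be expressed as a share of the planning effect of .37, because section 2.3 does not state the metric of that effect.

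The practical consequence is confined to the self-report follow-up. It is clearest at 3 months, where persistence is hypothesised, and applies also to the 12-month assessment. The rule should be changed, but nothing in the design or sample size has to change with it.

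**What to change.** Revise the missing-data paragraph of section 2.7, and any fuller analysis plan, as follows.

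- Keep the logistic regression only to describe who is missing and which observed variables predict it. Remove it as the test that selects the analysis.
- Use the REML mixed model, already planned, as the MAR analysis, and include the observed predictors of missingness in it.
- Run the pattern-mixture analysis, already named, on the 3- and 12-month self-report outcomes whatever the regression shows. A delta-adjusted version would do: shift the imputed values by a stated range, for example 0 to 0.75 SD in the unfavourable direction, and report where the conclusion changes.
- Keep the comparison of complete cases with imputed data if wanted, but do not present it as a check on MNAR.

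The cost is a few sentences and one additional sensitivity analysis to program. No further data collection or participants are needed.
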